[figure not shown]

**FOR RANDOMISATIONS**

**[contact]**

**Website: <https://www.trials.bham.ac.uk/stamp>**

## Protocol Versions

- 1.0 Submitted to MREC and MHRA
- 2.0 Incorporates MREC comments
- 3.0 Amendment Number 1 – Substantial – Date 16/11/2010
  - 3.1 Modification to Amendment Number 1 – in response to MREC comments - Date 05/01/2011
- 4.0 Amendment Number 2 – Substantial - change of PI at University Hospital of North Staffordshire NHS Trust – Date 22/11/2011
- 5.0 Amendment Number 3 – Substantial – Date 16/04/2012
- 6.0 Amendment Number 5 – Substantial – Date 18/01/2013
- 7.0 Amendment Number 7 - Substantial – Date 22/11/2013

## Abbreviations

|         |                                                                          |
|---------|--------------------------------------------------------------------------|
| AE      | Adverse event                                                            |
| AR      | Adverse reaction                                                         |
| ASR     | Annual Safety Report                                                     |
| BCTU    | Birmingham Clinical Trials Unit at the University of Birmingham          |
| CA      | Competent Authority                                                      |
| CI      | Chief Investigator                                                       |
| CTA     | Clinical Trial Authorisation                                             |
| DMEC    | Data Monitoring and Ethics Committee                                     |
| EDF     | End-diastolic flow                                                       |
| EudraCT | European Clinical Trials Database                                        |
| GCP     | Good Clinical Practice                                                   |
| GMP     | Good Manufacturing Practice                                              |
| GP      | General Practitioner                                                     |
| IMP     | Investigational Medicinal Product                                        |
| ISRCTN  | International Standard Randomised Controlled Trial Number                |
| MHRA    | Medicines and Healthcare Products Regulatory Authority                   |
| MRC     | Medical Research Council                                                 |
| MREC    | Multicentre Research Ethics Committee                                    |
| PE      | Pre-eclampsia                                                            |
| PI      | Principal Investigator – the local lead investigator for the StAmP Trial |
| PIGF    | Placental Growth Factor                                                  |
| PIS     | Participant Information Sheet                                            |
| QP      | Qualified Person for release of trial drug                               |
| RR      | Relative Risk                                                            |
| SAE     | Serious Adverse Event                                                    |
| SAR     | Serious Adverse Reaction                                                 |
| SCr     | Serum Creatinine                                                         |
| SEng    | Soluble Endoglin                                                         |
| sFlt-1  |                                                                          |
| SOP     | Standard Operating Procedure                                             |
| SmPC    | Summary of Product Characteristics                                       |
| SSAR    | Suspected Serious Adverse Reaction                                       |
| SUSAR   | Suspected Unexpected Serious Adverse Reaction                            |
| TMG     | Trial Management Group                                                   |
| TSC     | Trial Steering Committee                                                 |
| UCLHfT  | University College London Hospitals NHS Foundation Trust                 |

## 1. SUMMARY

Pre-eclampsia is a multi-system syndrome of pregnancy characterised by hypertension and proteinuria. Early onset pre-eclampsia, prior to 32 weeks' gestation, is associated with substantial morbidity and mortality for both mother and baby. As yet there is no effective treatment for pre-eclampsia other than delivery of the baby.

Recent research has identified that the placenta releases factors (anti-angiogenic factors) into maternal blood before the onset of pre-eclampsia. Initial studies suggest that statins can reduce the level of these factors, and perhaps reduce or eliminate the effects of pre-eclampsia.

This trial aims to establish whether pravastatin causes a significant reduction of these placental factors in women with early-onset pre-eclampsia. To test this hypothesis, we will ask the following questions:

1. Does pravastatin cause a greater inhibition of circulating placental factors in women with early-onset pre-eclampsia compared with placebo?
2. Are there any adverse or beneficial effects to the mother or the baby following gestational exposure to pravastatin during pre-eclampsia?
3. If pravastatin appears to safely inhibit circulating placental factors, how best can a substantive trial/health technology assessment be undertaken to develop guidance for routine use of statins to prevent or ameliorate pre-eclampsia?

StAmP is a double blind, placebo controlled multicentre randomised trial of pravastatin to ameliorate early onset pre-eclampsia.

Early-onset pre-eclampsia affects 1:200 primigravid pregnancies. In order to obtain the number of patients necessary even for this proof of principle trial of statins for the amelioration of pre-eclampsia, the trial will need the participation of several centres. To make this practicable, trial procedures need to be kept simple, minimising the bureaucratic burden on participating clinicians, using simple randomisation procedures and centralised coordination of trial drug packs.

## **2. BACKGROUND**

### **2.1. Pre-eclampsia**

#### **2.1.1. Clinical presentation**

Pre-eclampsia is a multi-organ syndrome of pregnancy that manifests after 20 weeks gestation with new-onset hypertension and proteinuria. Pre-term pre-eclampsia is associated with substantial morbidity and mortality for both mother and baby. Pre-eclampsia is defined as blood pressure  $\geq 140$  mmHg systolic and  $\geq 90$  mmHg diastolic diagnosed for the first time after 20 weeks' gestation together with  $>300$  mg proteinuria/24 hours. But this definition hides the multi-system nature of pre-eclampsia, which can cause liver dysfunction, renal impairment and maternal seizures. The fetus is often growth restricted and if born pre-term often struggles with the consequences of prematurity. A typical pre-eclamptic blood profile will show elevated serum creatinine and liver transaminases with consumption of platelets.

There is no widely accepted definition of severe pre-eclampsia. Nevertheless, early onset pre-eclampsia, before 32 weeks' gestation, is more likely to be associated with severe hypertension ( $\geq 160$  mmHg systolic or  $\geq 110$  mmHg diastolic), heavy proteinuria ( $>5$  g/24 hours), pulmonary oedema, raised liver transaminases, high serum creatinine (SCr  $>120$   $\mu$ mol/L), low platelets ( $<100 \times 10^9$ /l) and fetal growth restriction (1). Eclampsia manifests when seizures develop during or just after a pregnancy that has usually been affected by pre-eclampsia, but occasionally eclampsia is a presenting feature.

#### **2.1.2. Incidence**

Pre-eclampsia affects 3-5% of all first time pregnancies, but early severe pre-eclampsia occurs in only 1:200 pregnancies (2). The incidence of pre-eclampsia varies according to maternal risk factors, such as pre-existing chronic hypertension, obesity and diabetes. Approximately one quarter of pre-eclampsia cases are classed as either severe or early with 11% both early and severe (3). Women with pre-eclampsia are more likely to have a stillbirth or neonatal death (4).

Worldwide, hypertensive disorders of pregnancy, predominantly due to early, severe pre-eclampsia, account for a significant proportion of maternal deaths: a quarter of maternal deaths in Latin America (5) and 15% of direct maternal deaths in the UK (6).

#### **2.1.3. Risk factors**

Significant risk factors for pre-eclampsia include nulliparity, chronic hypertension, renal disease, diabetes, pre-eclampsia in a previous pregnancy, mothers older than 35 years, obesity, multiple pregnancy, and a birth interval  $>10$  years (7).

### **2.2. Current prevention and management strategies for pre-eclampsia**

Women are screened for the above risk factors for pre-eclampsia at their first antenatal visit. Subsequent antenatal assessments include monitoring for hypertension and proteinuria (8). New onset hypertension and proteinuria is then more thoroughly investigated for other organ involvement in pre-eclampsia.

Evidence for primary prevention strategies is equivocal, as both rest and exercise have been suggested in poor quality studies (9;10). It is also unclear whether dietary regimes have any significant effect on risk, although calcium supplementation reduces the relative risk (RR) of pre-eclampsia significantly (RR 0.48; 95% CI 0.33 to 0.69), particularly in high risk women or those with low calcium diets (11). Antioxidant vitamins C and E supplements have not shown to prevent pre-eclampsia in women at higher risk (12).

Antiplatelet drugs, principally low dose aspirin, reduces the relative risk of pre-eclampsia by 19% (RR 0.81, 95% CI 0.75 to 0.88) (11). Antihypertensives, nitric oxide and progesterones have not been shown to have any effect (13;14). Antihypertensives as treatment for mild to moderate mid-trimester hypertension reduce

blood pressure, but do not slow or prevent the progression to pre-eclampsia. Judicious use of beta blockers for the treatment of chronic hypertension have been shown to be more effective than methyldopa at reducing the risk of severe hypertension (RR 0.75; 95 % CI 0.59 - 0.94) (15).

Once pre-eclampsia is diagnosed, most existing treatments are symptomatic with little evidence that the underlying pathophysiology is arrested by intervention. Anti-hypertensive drugs are essential for severe hypertension ( $\geq 160$ mmHg systolic or  $\geq 110$ mmHg diastolic) (16), but there is insignificant evidence to indicate which drug is preferable (17). Prevention of eclampsia and prolongation of the pregnancy then becomes the focus of management. Robust evidence exists for the role of magnesium sulphate in the prevention of a first eclamptic seizure or eclampsia (18;19). Fluid restriction is advisable to reduce the risk of fluid overload (16). Birth of the baby after stabilisation of the mother is advised if the pregnancy is over 36 weeks' gestation (20). In early onset pre-eclampsia, clinical decisions need to be made that balance the benefits of immediate child-birth for the mother compared with the danger of complications of prematurity for the fetus. Where immediate child-birth is not essential, a delay of 24 hours will allow steroids to be given to mature the baby's lungs, although a shorter duration may still be of benefit (21). Expectant management of early onset pre-eclampsia (24-33 weeks) has been shown to improve neonatal outcome, with pregnancy prolonged for an average 7.1-15.4 days (22-27).

When managing severe pre-term pre-eclampsia, the incidence of neonatal prematurity-related co-morbidities gradually diminishes with increasing gestational age. Over 32 weeks gestation, neonatal benefits diminish compared with increasing maternal risks (23). Furthermore, induction of labour is less likely to be effective at an early gestational age, making Caesarean section more likely.

## **2.3. Statins in pre-eclampsia**

### **2.3.1. In vitro biomarker data**

Increasing evidence supports the premise that loss of vascular endothelial growth factor-A (**VEGF**) and/or placenta derived growth factor (PIGF) activity, due to an increase in the anti-angiogenic sFlt-1, which binds VEGF and PIGF, may lead to pre-eclampsia (28). sFlt-1 is increased in the maternal circulation in pre-eclampsia, even before onset of the clinical disease (29). Despite the multiple genotypes and phenotypes that underlie pre-eclampsia, it appears that serum levels of **PIGF**, sFlt-1 and soluble endoglin (**sENG**), give the highest strength of association with outcome (30;31). However, based on a recent systematic review, at present the evidence is insufficient to recommend these markers for screening (32). An elevated sFlt-1:PIGF ratio at 10-17 weeks gestation has been shown to be strongly associated with an increased risk of developing early onset, but not late-onset pre-eclampsia (33)

### **2.3.2. Ex vivo data**

Agents capable of inhibiting sFlt-1 may have the therapeutic potential to alleviate the severity of pre-eclampsia and in turn prolong pregnancy in early onset disease, so reducing the complication burden for both mother and neonate. Recently, we showed that statins (HMG-CoA reductase inhibitors), a class of lipid-lowering drugs, inhibit cytokine-mediated release of sFlt-1 and sEng (34). Based on our laboratory findings, statins offer a logical potential therapy.

### **2.3.3. Animal data**

Direct evidence that excess circulating sFlt-1 plays a role in the pathogenesis of pre-eclampsia is provided by studies in rats where administration of sFlt-1 or a VEGF neutralising antibody resulted in glomerular endothelial cell damage and proteinuria (35). Furthermore, adenoviral delivery of sFlt-1 to pregnant animals also mimics the clinical manifestations of pre-eclampsia (36). Our recent *in vivo* study shows that a reduction of circulating sFlt-1 by exogenous VEGF alleviates the pre-eclampsia-like signs of hypertension, proteinurea and glomerular endotheliosis in mice. Adenoviral (Adv) over-expression of sFlt-1 induced vascular damage of glomeruli, promoted proteinuria and caused a significant increase in blood pressure in

Balb/c mice. To rescue the damaging effects of AdsFlt-1, mice were co-administered AdvFlt-1 and AdvVEGF to mop up circulating sFlt-1. The detectable levels of free sFlt-1 were reduced by over 80% in plasma (from 74.4ng/ml to 12.1ng/ml). AdsFlt-1 mediated increase in urine protein albumin was dramatically reduced by AdvVEGF co-administration and sFlt-1 concentrations fell from 8ng/ml to 1.25ng/ml in urine samples collected at 24 hours. Furthermore, histopathological analysis confirmed almost no visible damage to the kidneys in the rescue experiments (37). This demonstrates that below a critical threshold sFlt-1 fails to illicit damage to the fenestrated endothelium and that co-expression of VEGF is able to rescue effects mediated by sFlt-1 over-expression. **Thus, reduction in sFlt-1 is a valid surrogate endpoint for a clinical outcome measure.**

Statins also improve factors that are compromised in pre-eclampsia such as nitric oxide (NO) bioavailability, VEGF and hemeoxygenase-1 (HO-1) expression as well as mobilising endothelial progenitor cells (34). Furthermore, statins substantially decrease cardiovascular morbidity and mortality outside of pregnancy (38). Finally, preliminary experiments show that simvastatin (0.5mg/kg) reduced sFlt-1 levels by over 80% in pregnant mice. **Our proposal represents a unique opportunity to test the hypothesis that a significant reduction of sFlt-1 by statin use will alleviate the signs of early onset pre-eclampsia.**

#### **2.3.4. Category X status – is this evidence based?**

If strong markets exist for the use of drugs in the non-pregnant state, such as statins, pharmaceutical companies rarely seek licenses for use in pregnancy. Currently, statins (HMG-CoA reductase inhibitors) are contraindicated in pregnancy – they have category X status. The US Food and Drugs administration define category X drugs as those where:

Studies in animals or humans have demonstrated fetal abnormalities and/or there is positive evidence of human fetal risk based on adverse reaction data from investigational or marketing experience, and the risks involved in use of the drug in pregnant women clearly outweigh potential benefits

Statins are contraindicated in pregnancy because:

- They have been associated with fetal skeletal malformations observed in rats given maternally toxic doses of a lipophilic statin, lovastatin (800 mg/kg daily) (39). **However, similar or even greater doses of (hydrophilic) pravastatin given to pregnant rats (up to 1000mg/kg/day) and estimated to be x120 human exposure based on surface area (mg/m^2) were not teratogenic (personal communication Bristol-Myers Squibb).**
- It is known that cholesterol and other products of cholesterol biosynthesis are essential components for fetal development. Because HMG-CoA reductase inhibitors such as pravastatin decrease cholesterol synthesis, they are contraindicated in pregnancy. Pravastatin has been included with the lipophilic statins in this regard.
- When statin treatment has been continued inadvertently in pregnant women (e.g. those with familial hypercholesterolemia) at therapeutic doses (20-80 mg/daily), there have been rare reports of congenital abnormalities exposed during the first trimester to lipophilic statins, but not with pravastatin (40). However, these rare adverse events were not more frequent compared with expected from a general pregnant population (41-47). It has been calculated that current evidence is only adequate to exclude a 3-4 fold increased risk of congenital abnormalities compared with a background risk. There is therefore a lack of evidence from any human study that can categorically reassure about the safety of statins given to pregnant women.

To further investigate the potential role of statins on adverse fetal outcome, we undertook a systematic review of all available published data of adverse fetal events following maternal use of statins during pregnancy. We also contacted pharmaceutical distributors of pravastatin, lovastatin and simvastatin for unpublished records of statin related anomalies. From the selected studies, we investigated the pregnancy

outcome of cases exposed to statins. From 550 women exposed to statins during pregnancy and after exclusions for confounders, a total of 19 cases had an adverse pregnancy outcome. Six of these pregnancies proceeded to elective abortion and were excluded from further analysis. Out of the remaining 13 cases with both adequate extractable data and free from confounding factors, one resulted in an intrauterine death, six had major fetal morbidity and six had minor adverse events. In all cases, statin use was limited to the first trimester, and all the final cases were exposed to either lovastatin (20-40mg) or simvastatin (10-20mg). Structural abnormalities such as polydactyly and cleft lip were the most common minor adverse events. Three out of 550 pregnancies exposed to simvastatin and lovastatin were affected by the VACTERL syndrome. This midline anomaly is compatible with interference with lipid metabolism. No abnormalities were observed from the 32 reported exposures to pravastatin (40;45;48).

Although 32 cases of pravastatin exposure in pregnancy is too few from which to draw reassuring conclusions, there are important reasons why pravastatin is likely to be different from other statins. Unlike other statins, pravastatin is hydrophilic not lipophilic (49) and therefore has much reduced tissue penetration, reducing its ability to cross the placenta (50).

We propose to use pravastatin 40mg only after 24 weeks' gestation, by which time most of the critical neural and cardiovascular development is complete. Our systematic review, plus the recent scientific literature, would suggest that if pravastatin were to be administered at the onset of pre-eclampsia, it may be of benefit to the mother and prolong the pregnancy without increased risk to the fetus.

## **2.4. The choice of questions to be asked**

### **2.4.1. Rationale**

The rationale for using statins to ameliorate pre-eclampsia is based on in vitro work that identifies a consistent activation of heme-oxygenase and suppression of sFlt-1 and sEng (anti-angiogenic factors elevated in pre-eclampsia) in cultured endothelial and trophoblast cells (34). For this reason we have chosen to use a measure of circulating maternal serum levels of sFlt-1 and sEng as primary endpoints. This trial is not powered to look at changes in clinical outcome, but differences in the length of pregnancy after randomisation will be used to inform the Data Monitoring Committee as to whether statins are clinically harmful.

The safety of statins in pregnancy is uncertain. Limited evidence on 550 women who inadvertently took statins in the first trimester shows no higher level of fetal abnormality than in the general population (see above). However 3 cases of VACTERL syndrome (out of 550), which is normally found in only 1:3500 pregnancies, raises suspicions that statins may interfere with midline development to cause this anomaly during the first trimester. We have chosen to limit this study to women with pre-eclampsia after 24 weeks gestation, away from the first trimester. There have been very few documented cases of women who have continued statins into the second and third trimesters, but there are no cases associated with fetal harm. Furthermore, we have chosen to study the effect of pravastatin, a hydrophilic statin, that unlike the other lipophilic statins will cross the placenta much less easily. There have been no reported cases of fetal harm out of 32 cases in which the mother took pravastatin in pregnancy.

**Early severe pre-eclampsia (24 to 31+6 weeks gestation) is a life-threatening condition for mother and offspring. Although we have minimised the risks to the fetus by studying women after 24 weeks gestation and using hydrophilic pravastatin, we feel the potential harm to the fetus of early severe pre-eclampsia is balanced by the potential benefits of identifying a disease-modifying drug.**

If our hypothesis is correct, and pravastatin is shown to safely suppress maternal sFlt-1 and sEng levels in women with pre-eclampsia, this trial will have informed a potential future study that could be powered to use pravastatin to prevent pre-eclampsia. Linked studies will measure pravastatin in the cord blood to identify whether this drug or its metabolites cross the placenta in significant amounts.

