## **2.5. Aims and objectives of this proof of principle trial**

The aim of the trial is to establish whether pravastatin will lead to a significant reduction of anti-angiogenic factors in women with early-onset pre-eclampsia. To test this hypothesis, we will ask the following questions:

1. Does pravastatin cause a greater inhibition of circulating anti-angiogenic factors in women with early-onset pre-eclampsia compared with placebo?
2. Are there any adverse or beneficial effects to the mother or the baby following gestational exposure to pravastatin?
3. If pravastatin appears to safely inhibit circulating anti-angiogenic factors, how best can a substantive trial/health technology assessment be undertaken to develop guidance for routine use of statins to prevent or ameliorate pre-eclampsia?

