### **5.3. Randomisation method and stratification variables**

Participants will be randomised individually into the StAmP Trial in an equal ratio of pravastatin to placebo. A 'minimisation' procedure using a computer-based algorithm will be used to avoid chance imbalances in important stratification variables. Stratification variables will be:

- Gestation age at diagnosis (<30 weeks: ≥ 30 weeks)
- Smoking status (Current smoker, stopped when became pregnant, and non-smoker)
- Severity of pre-eclampsia, according to the American College of Obstetrics and Gynaecology criteria (>140mmHg systolic or 90mmHg diastolic but less than 160 or 110mmHg; greater or equal to 160 or 110mmHg)

Due to risk of foreknowledge, the randomisation will be balanced within a centre, rather than minimised by investigator.

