## **9. ACCRUAL AND ANALYSIS**

### **9.1. Sample size**

The sample size for this trial has been estimated using the hypothesis that statins will reduce sFlt-1 levels compared with placebo during the first 72 hours after onset of treatment. We have demonstrated that

statins inhibit sFlt-1 from  $18.0 \pm 0.4$  ng/ml to  $8.5 \pm 1.2$  ng/ml (mean  $\pm$  SD) within 24 hours in an *ex vivo* human placental model (34;56).

The level of sFlt-1 in a normal pregnant woman is  $19.3 \pm 15.5$  ng/ml and for those with pre-eclampsia around  $66.6 \pm 26.4$  ng/ml. Our studies suggest that with statin use sFlt-1 levels will be expected to halve, a reduction of over one standard deviation. To detect one standard deviation difference with 80% power and  $p < 0.05$  would require 34 patients in total at any one time point. For our primary analysis we shall be carrying out a repeated measures analysis assessing the effect over the first three days (1 reading available per day), including an adjustment for the baseline value. If we conservatively assume that the Intra-class Correlation Coefficient of these readings is 0.9, and additionally that the correlation with the baseline value is only 0.1, then the required sample size for this analysis is 32.

To allow for some women failing to provide all three days of sFlt-1 data, StAmP will aim to recruit **up to 64** participants in total.

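### With at most about 32 women on pravastatin, StAmP can report whether a safety signal was seen but cannot show safety, and the planned risk ratio and chi-squared test give no usable limit for rare harms

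*Combined protocol and SAP*

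**What the plan says.** **Safety wording.** Section 2.4.1 ends on the case where "pravastatin is shown to safely suppress maternal sFlt-1 and sEng levels in women with pre-eclampsia", and says that then "this trial will have informed a potential future study that could be powered to use pravastatin to prevent pre-eclampsia". Question 3 of 2.5 is softer: "If pravastatin appears to safely inhibit circulating anti-angiogenic factors, how best can a substantive trial/health technology assessment be undertaken". Question 3 of the Summary has the same softer form. No section defines *safely* by an event, a threshold or a margin.

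**Size.** Section 9.1: "StAmP will aim to recruit up to 64 participants in total". Section 5.3: "Participants will be randomised individually into the StAmP Trial in an equal ratio of pravastatin to placebo". The calculation in 9.1 concerns sFlt-1 only, and the rise from 32 to 64 is made "To allow for some women failing to provide all three days of sFlt-1 data". Section 2.4.1 says openly that there is no power for clinical outcome.

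**Earlier exposures.** Section 2.3.4 reports: "No abnormalities were observed from the 32 reported exposures to pravastatin". It then comments: "Although 32 cases of pravastatin exposure in pregnancy is too few from which to draw reassuring conclusions".

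**Planned safety analysis.** Section 8.2 lists serious adverse events and reactions as a secondary outcome. Section 7.1 counts maternal or fetal death, and congenital anomalies not seen before onset, as serious. Table 1 collects maternal mortality, neonatal mortality and congenital anomalies. Section 9.2 presents dichotomous outcomes as risk ratios with a chi-squared test, promises 95% confidence intervals in general, and leaves further detail to a later Statistical Analysis Plan.

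**The concern.** Question 2 of 2.5 asks whether mother or baby is harmed or helped by exposure to pravastatin. For rare, grave outcomes the likely counts in arms of about 32 are none or very few. The reader then needs to know how large a harm the data still allow. The planned risk ratio cannot supply that in the very case where the table looks clean, and *safely* in the Rationale invites the reader to take no observed harm as evidence of no harm.

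The drug is contraindicated in pregnancy, and 2.4.1 justifies fetal exposure because early severe pre-eclampsia is itself life-threatening. That balance does not carry over to women without disease, and item 4 of 2.6 says the pilot will inform the design of a study in asymptomatic women. A clean table without limits is easily over-read at that step.

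**Working it through.** **1. The plan's own sample size.** Inputs from 9.1 and 9.2: difference 1 SD, power 80%, two-sided alpha 0.05.
- Normal approximation: 2 × (1.96 + 0.84)² = 15.7 per arm, so 16 per arm and 32 in total.
- t-based: 16 per arm gives 78.1% power and 17 per arm gives 80.7%, so 34 in total, as stated.
- Repeated measures, three readings, intra-class correlation 0.9, baseline correlation 0.1: factor (1 + 2 × 0.9)/3 − 0.1² = 0.9233; 34 × 0.9233 = 31.4, so 32 in total, as stated.

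The figures reproduce. They concern sFlt-1 only.

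**2. Number exposed.** 64 × 1/2 = 32 at most. This is an arm size. It differs from the 32 that 9.1 gives as a total, and from the 32 earlier exposures in 2.3.4.

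**3. What no events would exclude.** The exact upper limit solves (1 − p)³² = tail probability.
- Two-sided 95%: 1 − 0.025^(1/32) = 10.9%.
- One-sided 95%: 1 − 0.05^(1/32) = 8.9%.
- With only 24 women on pravastatin (illustrative): 14.2% and 11.7%.
- Adding the 32 earlier exposures (0/64): 5.6% and 4.6%, though timing of exposure may differ.

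**4. Chance of a clean arm despite real harm.** The documents give no event rates, so these are assumed; the chance of no event is (1 − p)³².

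| True rate | No event in 32 |
|---|---|
| 1% | 72% |
| 3% | 38% |
| 5% | 19% |

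**5. Comparison between arms.** Rates again assumed, 32 per arm: power is 11% for 5% v 10%, 20% for 10% v 20%, and about 81% only for 10% v 40%.

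**6. How the 9.2 method behaves.**
- No events in either arm: the risk ratio is 0/0, and there is no interval.
- No events in one arm: the ratio is 0 or infinite, and the usual log-scale standard error contains 1/0.
- Sparse counts: with k events in total and 32 per arm, the expected count per arm is 32k/64 = k/2, below the conventional 5 whenever there are fewer than 10 events.
- Example, 5/32 v 0/32. Chi-squared (uncorrected) = 64 × (5 × 32 − 0 × 27)² / (32 × 32 × 5 × 59) = 5.42, p = 0.020. Fisher's exact two-sided p = 2 × C(32,5)/C(64,5) = 2 × 201,376/7,624,512 = 0.053. The two tests fall on opposite sides of 0.05.

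**The case against.** The case against is substantial, and most of it stands.

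- **The wording is mostly hedged already.** A reader might infer that the objectives let the trial declare pravastatin safe and move on. They do not. The firm wording is in one conditional Rationale sentence, while the Summary and 2.5 speak only of appearance. Section 2.4.1 also calls the safety of statins in pregnancy uncertain.
- **Moving on means further trials.** Section 2.6 has the substantive trial ask for adverse-effect rates itself. Nothing in 9.2, 10.3 or 11.9 provides for a claim of demonstrated safety.
- **Item 4 of 2.6 is not conditional on safety.** It says only that the pilot informs a study design. A reader might take it as resting on a clean StAmP result, but the text does not say so.
- **Matching counts do not make matching evidence.** It is tempting to say that the protocol condemns its own safety data, since it calls 32 exposures too few. That remark concerns earlier, uncontrolled reports and fetal abnormality. StAmP's women are exposed after 24 weeks, with a randomised placebo arm and prospective collection of events. The evidence is better in kind; what carries over is the precision that a count of 32 allows.
- **Zero events is not the expected result for every outcome.** The protocol describes substantial mortality in this disease, so some perinatal deaths may occur. A single-arm limit cannot separate drug from disease; the comparison between arms does that.
- **Much is already in place.** The outcomes are collected, 95% intervals are promised in general, the DMEC reviews safety every three months, and a detailed analysis plan is to follow.

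What this leaves untouched is narrow. The method named in 9.2 fails or is unreliable for zero and sparse counts, and DMEC review protects participants without settling what the final report may say.

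**Conclusion.** The point holds in a limited form and is minor. With at most about 32 exposed women, StAmP can report whether a safety signal was seen. It cannot show that pravastatin suppresses sFlt-1 *safely*, since 0/32 leaves a true rate of up to 10.9% open (two-sided 95%, matching the two-sided convention of 9.2; 8.9% one-sided). The analysis named in 9.2 would not convey this to the reader for rare outcomes.

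The limits assume full recruitment of 64 and an even split; fewer treated women would widen them. The power figures and the chances of a clean arm rest on assumed event rates. The documents do not support the stronger conclusion that the trial is set up to claim proven safety, or that its controlled safety data are worth no more than the earlier case reports.

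**What to change.** 1. **Section 9.2 (or the Statistical Analysis Plan).** Report fetal death, neonatal death, congenital anomaly and maternal death by arm, each with exact two-sided 95% limits, including where the count is zero. Add an exact interval for the between-arm risk difference. Use an exact test in place of chi-squared where counts are sparse, and state in advance what counts as sparse.
2. **Section 2.4.1.** Replace the phrase about being shown to suppress the markers safely with wording such as: suppresses sFlt-1 with no safety signal seen, within the stated confidence limits. Do not write a hypothetical 0/32 result into the objectives; the limits should come from the observed counts and the number actually recruited.
3. **Section 2.4.1 or 2.6.** State that a clean result does not by itself establish safety in asymptomatic women.

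Cost: one sentence reworded, one added, and a few more columns in the safety table, from data already collected under 7.1 and Table 1. The safety statement becomes less favourable. No extra women are needed, and the design, sample size and primary analysis are unaffected.
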